## 6.6 Assessment visit

The summary table is described in appendix 2.

### 6.6.1 Inclusion examination

Patients eligible for the trial and having signed their consent to participate shall have an initial assessment within the 21 days preceding the treatment start.

 Clinical examination

- Weight, height, performance status or WHO (appendix 3)
- Digital rectal exam
- Cardiovascular risk factors (HBP, hypercholesterolemia, diabetes, stress)
- Prior medical and surgical history
- Disease history
- Tobacco use

 Blood tests

- CBC - Platelets

- Prothrombin rate, TCA, INR

- Urea, creatinine

- Tumor marker: PSA

 Paraclinic tests

- Tumor evaluation by pelvic spiral CT (could be the planning scanner) and pelvic and prostatic MRI
- Planning CT-Scan (1)
- Bone scan

 Questionnaires

- Sexual quality of life “IIEF-5” (appendix 11)

- Urinary difficulty “IPSS” (appendix 12) score >10 is an exclusion criteria

 Disease classification

- Gleason score, number of positive biopsies and total length of positive biopsies (appendix 5)

1. *For dosimetry, the planning scanner will be conducted with the most informative sequences identified by the diagnostic scanner and fused with the MRI.*

### 6.6.2 Evaluation during treatment

Evaluation of tolerance according to the NCI-CTC AE v.3.0, weekly during conformal radiotherapy (first treatment phase) then before each stereotactic radiotherapy session.

***The following evaluation will be done before starting the hypofractionated stereotactic boost :***

 Clinical examination

- Weight, performance status or WHO (appendix 3)
- Digital rectal exam

 Blood tests

- Urea, creatinine
- Tumor marker : PSA

### 6.6.3 Post-treatment visit

Evaluation will be done 3 months after the last radiotherapy session :

 Clinical examination

- Weight, performance status WHO (appendix 3)
- Digital rectal exam
- Evaluation of acute toxicity related to irradiation

 Blood tests

- Urea, creatinine

- Tumor marker: PSA

 Paraclinic examination

- Prostate and pelvis MRI

 Questionnaires

- Sexual quality of life “IIEF-5” (appendix 11)

- Urinary discomfort “IPSS” (appendix 12)

### 6.6.4 Follow-up visit

Evaluation will be done 6, 9, 12, 18, 24 and 30 months after the last radiotherapy session :

 Clinical examination

- Weight, performance status or ECOG (appendix 3)
- Digital rectal exam
- Evaluation of late toxicity associated with irradiation

 Blood tests

- Tumor marker: PSA

 Paraclinic examinations

- Prostate and pelvis MRI (at 6, 12 and 24 month)

 Questionnaires

- Sexual quality of life “IIEF-5” (appendix 11)

- Urinary discomfort “IPSS” (appendix 12)

### 6.6.5 End of study evaluation

Evaluation will be done 36 months after the last radiotherapy session or at premature end from the study (see chapter 6.5).

 Clinical examination

- Weight, performance status or ECOG (appendix 3)
- Digital rectal exam
- Evaluation of late toxicity associated with irradiation

 Blood tests

- Tumor marker: PSA

 Laboratory and special studies/tests

- Prostate and pelvis MRI

 Questionnaires

- Sexual quality of life “IIEF-5” (appendix 11)

- Urinary difficulty “IPSS” (appendix 12)

### 6.6.6 Long term evaluation

Long term evaluation will be identical to the follow-up evaluation (see chapter 6.6.4) and will be done 48 and 60 months after the last radiotherapy session.

## 6.7 Assessment Criteria

### 6.7.1 Tolerance evaluation

Acute tolerance ( 6 months from the end of radiotherapy) and late effects associated with radiotherapy (> 6 months, from the end of radiotherapy) will be assessed according to the NCI-CTCAE scale, version 3.0 (appendix 10), from the data collected by the clinician.

#### Non-serious adverse events

Adverse event refers to any change in the initial condition of the patient prior to treatment, including intercurrent diseases, whether the event is considered as being related to irradiation or not and occurring at any time during the study.

The nature of each adverse event is established, along with the date of occurrence, duration, severity, relationship to treatment, associated treatments and outcome. The intensity of adverse events will be graded according to the criteria defined for the disease studied (NCI-CTCAE version 3.0 criteria – appendix 10).

#### Serious Adverse Events

Definition:

Not considered as a serious adverse event (SAE):

- Hospitalization < 24 hours (medical imagery examination, blood test, for example…)
- Planned hospitalization prior to the start of the trial and/or planned in the protocol

*The term serious adverse event (SAE) refers to any event:*

- Leading to death,
- Life threatening,
- Leading to hospitalization, or prolongation thereof,
- Causing permanent disability or serious temporary impairment,
- Causing a congenital abnormality, fetal malformation, or abortion,
- Medically significant.

The terms *disability* and *impairment* correspond to any clinically significant temporary or permanent physical or psychological handicap impacting the patient's physical activity and/or quality of life.

Any clinical event or laboratory result is considered *medically significant* if it is considered serious by the investigator and does not correspond to the above-defined seriousness criteria. These may represent a risk for the patient requiring medical intervention to prevent an outcome corresponding to one of the previously mentioned seriousness criteria *(*e.g., *overdosages, secondary cancers, and new facts that may be considered medically significant).*

#### *Serious adverse event - expected (SAE-E)*

A SAE-E is an event already mentioned in the results of studies with this type of treatment :

- Rectitis +/- hemorrhagic
- Cystitis +/- hemorrhagic

#### *Serious adverse event - unexpected (SAE-U)*

A SAE-U is an event other than those mentioned above or different in its nature, intensity, or development in regards to this list.

#### Intensity criteria

The intensity criterion must not be confused with the seriousness criterion, which serves as a guide to define declaration obligations.

The intensity of events will be estimated according to the NCI-CTCAE version 3.0 classification (toxicity grade 1 to 5). The intensity of unlisted adverse events in this classification will be estimated according to the following qualities :

**Mild** (grade 1): does not affect the patient's daily activity

**Moderate** (grade 2): disturbs the patient's daily activity

**Severe** (grade 3): prevents the patient's daily activity

**Very severe** (grade 4): requires reanimation measures / life threatening

**Death** (grade 5):

#### Steps to take

The investigator informs the Integrated Clinical Research Unit of all **Serious Adverse Events** whether or not they can be attributed to the research, which occur during the study or in the 3 months following the first irradiation session.

All late Serious Adverse Events (occurring after this 3 month period) considered as being reasonably related to the protocol treatment or to the research, must be declared without time limitation.

Declarations will be submitted by fax to the Clinical Research Unit using the "***serious adverse event notification***" form (appendix 10), documented in the most precise manner possible, dated and signed, within **24 working hours** of their observation, to :

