## 6.4 Early study withdrawal criteria

The length of patient participation in the study is at least 3 months after the last radiotherapy session.

The conditions for early termination of the study are :

- Failure to track the tumor
- Failure to place fiducial markers
- Dose-volume histograms (DVH) constraints not achievable
- Interval greater than 3 weeks between the end of the radiation therapy phase and the first session of hypofractionated stereotactic boost irradiation

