## 6.5 Termination study criteria

Termination from the study must take place if:

- disease progression

- patient’s decision

- investigator’s decision

- death of the patient

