### 6.8.4 Criteria for termination of the study

The study will be terminated if :

- a Grade 4 toxic event is observed according to the NCI scale,
- or a death in the 3 months following the last session of hypofractionated stereotactic boost irradiation

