**in 2/3 or 3/8 or 4/11 or 5/18 patients.**

# 7 TREATMENT

## 7.1 Patient enrollment

An inclusion request form will be completed by the investigator in order to ensure that the patient fulfils ALL selection criteria. The investigator must provide the information letter to the patient and have him sign the consent form making explicit its free and informed consent.

BEFORE INITIATING TREATMENT, the investigator must fax the inclusion request form to the Coor-dination Center of the study:

Clinical Research Integrated Unit / Promotion Section

Centre Oscar Lambret – Lille

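### The SAE reporting rule contradicts itself on unrelated events, and its 3-month clause ends before the stopping rule's death window does

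*Protocol*

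**What the plan says.** Three parts of the protocol bear on this.

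- **Reporting (6.7.1, Steps to take).** The investigator notifies all SAEs, attributable or not, "which occur during the study or in the 3 months following the first irradiation session", within 24 working hours. The next paragraph reads "All late Serious Adverse Events (occurring after this 3 month period) considered as being reasonably related to the protocol treatment" or to the research, and has these declared without time limit. The only 3-month period named before it runs from the first session.
- **Stopping (6.8.4).** The study stops for a Grade 4 toxic event "or a death in the 3 months following the last session of hypofractionated stereotactic boost irradiation", at the frequencies "in 2/3 or 3/8 or 4/11 or 5/18 patients". The death criterion carries no attribution filter.
- **Time on study.** Section 6.4 states: "The length of patient participation in the study is at least 3 months after the last radiotherapy session". Section 6.6.5 places the end-of-study assessment as follows: "Evaluation will be done 36 months after the last radiotherapy session or at premature end from the study". Section 6.5 lists the grounds for leaving, which include the patient's and the investigator's decision.

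**The concern.** The first sentence joins two limbs with *or*: an on-study limb and a limb of 3 months from the first session. Participation lasts at least 3 months beyond the last session, so the first-session limb adds nothing for a patient who stays on study. The second sentence nevertheless uses that shorter limb to mark where late events begin. An investigator with an unrelated death four months after the first session finds it reportable under one sentence and, under the next, a late event that is called for only if related.

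This matters because a stopping rule depends on the reporting rule. The boundaries are small counts, so one event not notified promptly can decide whether a boundary is seen to be crossed. SAE notification is the fast route. After the last boost, the next scheduled visit is at 3 months (6.6.3), when the death window is closing. The stopping rule counts every death, while the reporting rule can be read as making notification depend on a judgement of relatedness.

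**Working it through.** **Inputs**

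- First phase: 31 to 42 days (Appendix 1).
- Boost starts within 10 days of the last first-phase session and is delivered over 5 to 9 days (7.3).
- Longest interval before early withdrawal: 3 weeks, i.e. 21 days (6.4).
- Assumptions: 3 months = 91 days; the boost starts on the day after the first phase at the earliest.

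**Check of the protocol's own figures.** At five sessions a week, 20 of the 23 fractions are given by day 26 (D1–5, D8–12, D15–19, D22–26) and the last three on D29–31. The first phase therefore ends on day 31, as stated. Three boosts at 48-hour intervals need 1 + 2 + 2 = 5 days, also as stated.

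**Formulas**

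- Day of last boost L = first-phase days + gap + boost days − 1
- End of the first-session clause = 1 + 91 = day 92
- End of the stopping window = L + 91
- Days of the stopping window beyond the first-session clause = (L + 91) − 92 = L − 1

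**Results**

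| Schedule | L | Stopping window ends | Days beyond day 92 | Share of 91 days |
|---|---|---|---|---|
| Shortest: 31 + 1 + 5 − 1 | 36 | 127 | 35 | 38% |
| Longest standard: 42 + 10 + 9 − 1 | 60 | 151 | 59 | 65% |
| 3-week gap: 42 + 21 + 9 − 1 | 71 | 162 | 70 | 77% |

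The first-session clause thus reaches only 56 days (91 − 35), 32 days (91 − 59) or 21 days (91 − 70) past the last boost.

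**Who is affected**

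1. *Related death, any time:* reportable without time limit. No gap.
2. *Unrelated death, patient on study, first sentence read literally:* reportable. No gap, because 6.4 carries participation to at least the end of the stopping window.
3. *Unrelated death, patient on study, second sentence read as a limit:* not reportable after day 92. Gap as in the table.
4. *Unrelated death after premature exit (6.5, 6.6.5):* the on-study limb no longer applies and the first-session limb ends on day 92. Same gap, whichever way the second sentence is read.

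**After the change.** If the 3-month clause runs from the last session, its end coincides with that of the stopping window in every schedule, and the uncovered interval is 0 days.

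**The case against.** The strongest reply is that the text, read literally, leaves little open. The two limbs form a union and the on-study limb is the wider one. The second sentence contains no word such as *only* and can be read as extending the duty for related events rather than withdrawing it for others. For a patient on study, every death that counts for stopping is then already notifiable. This stands. A reader might infer from the first-session anchor that all-cause reporting as a whole stops 3 months after the first session, so that stopping-rule deaths generally go unreported. The documents do not support that, because it ignores half of the sentence.

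Two further points also stand in part. The early-exit case is narrow: several withdrawal grounds in 6.4 (marker placement failure, unachievable dose-volume constraints, more than 3 weeks before the boost) arise before any boost, so no post-boost window opens, and 7.5 keeps patients with distant progression in the study. Deaths are also captured elsewhere, through adverse event collection at visits, the 3-month visit, and date of death from any cause for survival (6.7.2). None of these has the 24-working-hour deadline that a stopping rule with small counts needs.

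What the reply does not remove is the conflict itself. If the on-study limb governs, defining late events from the first session serves no purpose for patients on study. The reply also gives no cover after premature exit.

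**Conclusion.** The point holds in a limited form. The reporting section contradicts itself on unrelated SAEs after 3 months from the first session, and its 3-month clause is anchored to a different session from the stopping rule's death window. Under the restrictive reading, or after premature exit, the last 35 to 59 days of that window (38% to 65%) lie outside mandatory all-cause notification, or 70 days (77%) at the 3-week limit. These figures rest on 91 days for 3 months and on the protocol's own schedule.

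The percentages are shares of calendar time. A reader might take them as the share of qualifying deaths that would be missed; the documents give nothing from which to estimate that share. Nor do they show that any death would be missed, only that the text can be read as not requiring prompt notification.

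**What to change.** Reconcile Steps to take in 6.7.1 with 6.4 and 6.8.4:

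1. Keep all-cause SAE reporting for the whole time the patient is on study.
2. Run the 3-month clause from the last irradiation session, and state that it applies after premature exit as well, so that it covers at least the death window of 6.8.4. The last session is never earlier than the first, so no patient's reporting period gets shorter.
3. Define late SAEs, for which relatedness is the criterion, as those after both periods have ended.

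Part 1 has to stay. Applying the relatedness criterion as soon as the re-anchored 3 months end would cut the all-cause reporting that the text now literally requires on study, up to the 36-month assessment.

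The change touches no dose, clinical rule or stopping threshold. It costs a few sentences and a few more SAE forms, mainly for patients who leave early.

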#### [contact] - [contact]

The investigator must also, whenever possible, attach the following documents to the serious adverse event report:

- A copy of the hospitalization record, or hospitalization prolongation record,
- A copy of the autopsy report,
- A copy of the results of all additional examinations performed, including any pertinent negative results, appending the laboratory's normal values.
- Any other documents deemed useful and relevant.

All of these documents must be anonymous.

Additional information may be requested (by fax, phone, or during a visit) by the monitor.

#### SAE monitoring

The investigator is responsible for providing appropriate medical monitoring of patients until the event is resolved or stabilized, or until the patient's death. **This may occasionally require monitoring after the patient's exit from the trial.**

He/she transmits the additional information to the Clinical Research Unit by means of an SAE declaration form (ticking the Follow-up N° X box to state that it is a follow-up and not an initial report) within 24 hours of receiving it. He/she also transmits the last follow-up on resolution or stabilization of the SAE.

He/she keeps all relevant documents concerning the presumed adverse event in order to be able, if necessary, to complete any previously transmitted information.

He/she responds to any additional information requests from the Clinical Research Unit's PV in order to document the initial observation.

6.7.2 Evaluation of tumor efficacy

To be deemed assessable, patients must have received **at least 1 session of boost stereotactic irradiation**.

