| **ASSESSMENT CRITERIA** | Primary  Urinary or rectal toxicity: According to the NCI-CTCAE v3.0 rating scale (appendix 10). Acute toxicities are defined as all toxicities occurring in the 6 months following the start of radiotherapy. Late toxicities are defined as all toxicities occurring beyond 6 months.  **Secondary**   - Rate of local control at 3 years: non progression of : - PSA level according to the Phoenix definition (nadir to be obtained) - Clinical examination (rectal touch) - No pathological signal on MRI - Median time without progression for the entire cohort: interval between the date of inclusion and the date of progression, whether clinical (rectal touch) or radiological (prostatic MRI). - Median overall survival: Median time for the entire cohort comprising the time between the date of inclusion and the date of death, whatever the cause. - Survival without biological failure at 3 years: Phoenix criteria for PSA increase (nadir + 2 ng/ml) (see chapter 6.7.3) - Technical criteria: Implantation of markers, treatment time, cumulative dosimetry, administration and length of boost session - PSA kinetics during the entire treatment (between the two irradiation phases) and after treatment - Sexual dysfunction = international questionnaire IIEF 5 - Urinary discomfort = IPSS questionnaire |
| **STATISTICAL ANALYSIS** | The initial characteristics of included patients will be presented in the form of summary tables. Continuous variables will be summarized by conventional descriptive statistics parameters (median and outlying  values, mean and standard deviation when necessary). Category variables will be presented in the form of contingency tables (absolute frequency and percentage of each modality), additionally stating the number of missing data, along with the 95% confidence interval.  Subject inclusion and exclusion criteria will be checked against data entered into the case report forms when possible. Any deviations from the protocol will be documented.  Survival will be analyzed by the Kaplan-Meier nonparametric method. |

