#### *Global survival*

Time between :

- inclusion date,
- date of death, whatever the cause,
- Patients alive at the time of the analysis will be censored at the date of the last follow-up visit.

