#### *Survival without metastatic disease*

Time between:

- inclusion date,
- date of appearance of the first metastasis.

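### Efficacy is limited to men who had a boost session, but survival is timed from inclusion; if that rule governs, overall survival carries a small amount of guaranteed time, and the synopsis names a different population

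*Protocol*

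**What the plan says.** Protocol section 6.7.2 (Evaluation of tumor efficacy) opens with a rule for who can be assessed: the man must have had "at least 1 session of boost stereotactic irradiation". Two time-to-event endpoints are then defined under that heading. Global survival runs from inclusion to the "date of death, whatever the cause". Survival without metastatic disease runs from the "inclusion date" to the "date of appearance of the first metastasis".

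The synopsis (Assessment criteria) defines time without progression as the "interval between the date of inclusion and the date of progression", again for the whole cohort. It gives overall survival as "Median time for the entire cohort comprising the time between the date of inclusion and the date of death, whatever the cause". It has no matching definition for survival without metastatic disease.

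Section 6.8.2 says that survival will be analysed by Kaplan-Meier. It names no analysis set, landmark or delayed entry.

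Section 6.4 foresees men who leave before the boost. The reasons are failure to track the tumour, failure to place markers, unachievable dose-volume constraints, or an "Interval greater than 3 weeks between the end of the radiation therapy phase and the first session of hypofractionated stereotactic boost irradiation".

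**The concern.** Entry to the efficacy set depends on something that happens after inclusion, while the clock starts at inclusion. A man who dies between the two dates never enters the set. Every man who does enter is credited with having survived that interval. This is immortal time, and in a Kaplan-Meier curve drawn from inclusion it pushes overall survival upward.

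The two descriptions of the population also disagree. One analyst could follow 6.7.2 and use boosted men only. Another could follow the synopsis and use everyone included. Both would be following current text, and they would report different denominators for the same endpoint.

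**Working it through.** **The plan's own figure.** The protocol gives no expected rate or sample size for any survival endpoint. Its only sample-size figure is for toxicity (section 6.8.3): 76 evaluable men, from rates of 85% and 95%, 5% error and 90% power. It reproduces with a one-sided 5%:

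n = [(1.645 × √(0.85 × 0.15) + 1.282 × √(0.95 × 0.05)) / 0.10]² = 75.1, rounded up to 76.

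I use 76 below only to scale the standard error.

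**Time from inclusion to first boost.** Inputs:
- 0 to 21 days from initial assessment to treatment start (6.6.1), taking that assessment as the time of inclusion
- 31 to 42 days of first-phase radiotherapy (Appendix 1)
- boost start within 10 days of the last first-phase session (7.3), or up to 21 days before the withdrawal condition in 6.4 applies.

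Results:
- Shortest: 0 + 31 + 1 = 32 days (4.6 weeks). This assumes inclusion on the day treatment starts. If the 7-day wait between marker placement and planning CT (Appendix 6) falls after inclusion, it is 39 days (5.6 weeks).
- Longest on schedule: 21 + 42 + 10 = 73 days (10.4 weeks).
- At the three-week limit: 21 + 42 + 21 = 84 days (12 weeks).

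**Effect on 3-year overall survival.** Assume a constant hazard, true 3-year survival S, and t0 days from inclusion to first boost. A set made up only of men alive at t0 has expected 3-year survival

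S* = S / S(t0) = S^(1 − t0/1095).

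| Assumed S | t0 = 32 d | t0 = 73 d | t0 = 84 d | Standard error, √(S(1−S)/76) |
|---|---|---|---|---|
| 90% | +0.28 | +0.63 | +0.73 | 3.4 |
| 95% | +0.14 | +0.33 | +0.37 | 2.5 |

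All entries are percentage points. The on-schedule range is therefore about 0.1 to 0.6 points. As a wider check with 10 weeks of guaranteed time, the inflation is about 0.1 points at a true 98% and 1.2 points at a true 80%. The standard errors there are 1.6 and 4.6 points.

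**Omitted early deaths are the same effect.** The expected number of deaths before the boost at S = 90% and t0 = 73 days is 76 × (1 − 0.90^(73/1095)) = 0.53. Since S* − S = S* × (1 − S(t0)), leaving those deaths out raises the estimate by 0.906 × 0.53 / 76 = 0.0063. This is the same 0.63 points as in the table. A single omitted death is worth up to 1/76 = 1.3 points if it occurs, but that must not be added on top.

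**Progression and metastasis.** Section 6.6.2 schedules a rectal examination before the boost, and the synopsis counts progression by rectal examination, so an event can be found and dated in this window. Section 6.5 lists progression as a reason to leave the study, whereas 7.5 keeps a man with distant progression in it. The conditions in 6.4 do not mention progression. An early event may therefore remove a man from the boosted set, but no passage says that it must.

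**The case against.** The strongest reply is that 6.7.2 defines who is assessable but does not say that men without a boost are dropped from the Kaplan-Meier analysis. The synopsis already words two of the endpoints for the whole cohort from inclusion, and analysis sets are commonly fixed in an analysis plan that is not shown here. This stands in part: the bias arises only if 6.7.2 takes precedence. But the rule sits at the head of the section that defines overall and metastasis-free survival, and it conflicts with the synopsis. That is a contradiction in current text and not a detail left for later.

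A reader might also infer three stronger claims, none of which the protocol supports:
- *All three endpoints carry guaranteed event-free time.* This is strict for death only. For the other two, sections 6.6.2 and 7.5 leave room for an early event to be recorded in a man who still goes on to the boost.
- *The restriction must always favour the regimen.* The stated routes to no boost are mainly technical: those in 6.4, untrackable tumours (7.3.2) and prostate movement above 5 mm (7.3.1). That is a separate selection of unknown direction, so the net direction is not established.
- *Each omitted early death adds a further 1.3 points.* This counts one mechanism twice, as shown in the working.

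The objection that the effect is small also stands. These are secondary endpoints with no stated hypothesis or threshold.

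**Conclusion.** The mismatch is real, and its consequence is small. If 6.7.2 governs, overall survival timed from inclusion contains about 5 to 10 weeks of guaranteed time (12 at the outer limit). Under a constant hazard and an assumed true 3-year survival of 90% to 95%, this inflates the 3-year estimate by about 0.1 to 0.6 points in total, well below one standard error. For metastasis-free survival and time without progression, the effect probably applies only in part. Survival without biological failure is outside this point, because the protocol gives no start date for it.

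The toxicity test, its cut-off of 70 of 76 and the sample size are unaffected. What needs settling is which population the survival endpoints describe. Low priority.

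**What to change.** Reconcile 6.7.2 with the synopsis in one or two sentences. Overall survival, survival without metastatic disease and time without progression are analysed in all included men from inclusion. Any result restricted to men with at least one boost session starts the clock at the first boost session.

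The second part uses treatment dates that the trial will hold and needs no extra follow-up. Nothing changes in treatment, visits or sample size.

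There are two costs. The estimates become slightly less favourable. In the all-included analysis, men withdrawn under 6.4 may be censored early, because no continued follow-up is specified for them and the premature-exit evaluation in 6.6.5 refers only to exits under 6.5. The report should state how many men this affects.
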